#### Statistical Approach

#### Objective 1

A within-participant, longitudinal design will be used in which all veterans will first receive sham rTMS followed by active rTMS applied to the customized neural target and the standard FDA-approved treatment site (left DLPFC). Thus, there will be 2 groups. The primary outcome, functional disability (WHODAS 2.0), will be assessed at baseline, after sham rTMS, and after active rTMS. A mixed effects model, incorporating within-participant correlation from repeated measures, will be used to compare the difference between difference between sham (Figure 4: PS-BL) and active rTMS (Figure 4: PA-PS) treatments. We will compare the aforementioned difference in sham and active rTMS of the left DLPFC neural target or site of stimulation with the customized neural target group.

#### Objective 2

A recovery curve will be constructed based on repeated functional disability (WHODAS 2.0) measures at post–active rTMS, 2-week, 1-month, 3-month, and 6-month follow-up time points (Figure 4: PA, F1–F4). A mixed effects model (incorporating within-participant correlation from repeated measures) will be used to examine change (using the slope of the model) in WHODAS 2.0 from post–active rTMS to each follow-up time point for each group. We will examine the change in slope of the left DLPFC group compared to the customized neural target group using WHODAS 2.0 measures from post–active rTMS to each follow-up time point.

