### Objectives

This study aims to (1) test the preliminary efficacy of high-frequency rTMS provided to a customized neural target to treat functional disability among veterans with AUD+mTBI and (2) assess the sustainability of rTMS effects on functional disability among veterans with AUD+mTBI.

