## Discussion

### Hypothesized Principal Findings

For objective 1, addressing preliminary rTMS efficacy, we hypothesize that veterans receiving active rTMS at the customized site will have significantly improved functional disability from before to after active rTMS compared to from before to after sham rTMS and compared to the Beam F3 left DLPFC site. This will be indicated by a significantly lower or improved WHODAS 2.0 total complex score from before to after active rTMS compared to from before to after sham rTMS and compared to the Beam F3 left DLPFC site.

For objective 2, addressing rTMS sustainability, we hypothesize that veterans with AUD+mTBI receiving active rTMS applied to the customized site will sustain improvements in functional disability 2 weeks, 1 month, 3 months, and 6 months after active rTMS and that these improvements will be sustained beyond those sustained with rTMS applied to the Beam F3 left DLPFC site.

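### Objective 2 compares the arms only on change after the post-active visit, which measures loss of effect and does not test the hypothesis of larger retained improvement at the customized site

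*Protocol article*

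**What the plan says.** The Objectives section gives the second aim as to "assess the sustainability of rTMS effects on functional disability among veterans with AUD+mTBI". The Discussion (Hypothesized Principal Findings) makes this specific in two parts. Veterans treated at the customized site "will sustain improvements in functional disability 2 weeks, 1 month, 3 months, and 6 months after active rTMS", and "these improvements will be sustained beyond those sustained with rTMS applied to the Beam F3 left DLPFC site".

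The analysis is in Statistical Approach, Objective 2. The recovery curve uses repeated "measures at post–active rTMS, 2-week, 1-month, 3-month, and 6-month follow-up time points (Figure 4: PA, F1–F4"). A mixed effects model "will be used to examine change (using the slope of the model) in WHODAS 2.0 from post–active rTMS to each follow-up time point" in each group, and the between-arm step is "We will examine the change in slope of the left DLPFC group compared to the customized neural target group", again measured from PA. The baseline (BL) and post-sham (PS) visits do not appear in this analysis.

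Only Objective 1 uses the visits before active treatment. It contrasts "sham (Figure 4: PS-BL) and active rTMS (Figure 4: PA-PS) treatments", compares that contrast between sites, and stops at PA. Nothing in the article joins the two analyses or makes Objective 2 conditional on the result of Objective 1.

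**The concern.** An improvement is a change from the state before active treatment. The hypothesis is that this change persists and is larger in one arm. The planned contrast takes PA as its starting point, but PA is itself an outcome of the treatment being compared. The contrast therefore describes how much of the effect is lost after treatment ends, and not how much remains.

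The two can disagree. An arm that gained nothing has nothing to lose, so it gives a flat line. An arm that gained more has more room to drift back. Objective 1 predicts that the customized arm will have the larger gain at PA, so the conflict becomes more plausible if the investigators' own first hypothesis is right. At stake is the sign of the reported site difference for the second objective, and the estimate that a larger trial would take forward.

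**Working it through.** **1. What each contrast contains.** Let D(k) be the between-arm difference (customized minus left DLPFC) in change from the pre-active level at visit k. Lower WHODAS 2.0 is better, since the Discussion describes success as a "significantly lower or improved WHODAS 2.0 total complex score from before to after active rTMS". Then

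D(k) = D(PA) + [difference between arms in change from PA to k].

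The hypothesis concerns D(k) at F1–F4. Objective 2 estimates only the bracketed term. Objective 1 bears on D(PA), but as (PA−PS) against (PS−BL), so it is not the same quantity. No named contrast estimates the sum.

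**2. The level at PA drops out.** The least-squares slope is Σ(t−t̄)y / Σ(t−t̄)². Adding a constant c to every visit in one arm adds cΣ(t−t̄) = 0 to the numerator. For visit-wise changes, (y_k + c) − (y_PA + c) = y_k − y_PA. Neither version depends on how much the arm had gained by PA. This is algebra and needs no assumed data.

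**3. Illustration.** The article gives no WHODAS means, so these are assumed changes from the pre-active level.

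| Visit | Months from PA | Customized | Left DLPFC | Difference | Customized, from PA | Left DLPFC, from PA |
|---|---|---|---|---|---|---|
| PA | 0 | −8 | −3 | −5 | 0 | 0 |
| F1 | 0.5 | −7 | −3 | −4 | +1 | 0 |
| F2 | 1 | −6.5 | −3 | −3.5 | +1.5 | 0 |
| F3 | 3 | −6 | −3 | −3 | +2 | 0 |
| F4 | 6 | −6 | −3 | −3 | +2 | 0 |

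- t̄ = 10.5/5 = 2.1; Σ(t−t̄)² = 4.41 + 2.56 + 1.21 + 0.81 + 15.21 = 24.2.
- Customized numerator: 16.8 + 11.2 + 7.15 − 5.4 − 23.4 = 6.35, so the slope is 6.35/24.2 = +0.26 points per month. The left DLPFC slope is 0.
- Visit-wise changes from PA give the same sign: +1 to +2 against 0.
- Retained improvement points the other way: −4, −3.5, −3, −3 at F1–F4, average −13.5/4 = −3.4. At 6 months the identity in step 1 gives −5 + 2 = −3.

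The planned comparison favours left DLPFC although that arm is worse at every visit.

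**4. Would the reversal reach significance?** This depends on assumptions. Take SD 12–16, between-visit correlation 0.6–0.8 (compound symmetry) and 23 per arm (46/2). The standard error of the slope difference is SD·√(1−ρ)·√(2/23)/√24.2.

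- SD 12, ρ 0.8: 0.32, so z = 0.26/0.32 ≈ 0.8.
- SD 16, ρ 0.6: 0.61, so z = 0.26/0.61 ≈ 0.4.

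The chance of a significant result is then about 7–13%, so the likely report is no difference in slope.

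A more extreme assumed case has a PS mean of 38 in both arms, customized means of 24, 24.5, 25, 27, 30 at PA and F1–F4, and left DLPFC at 36 throughout. The slopes are +1.0 and 0, while the customized arm is better by 12, 11.5, 11, 9 and 6 points. In 5,000 simulated trials per setting (23, 18 or 13 per arm, same SD and correlation ranges, t-test on per-participant slopes), the slope pointed to left DLPFC in 89–100% of trials, significantly so in 21–86%. The F1–F4 average change from PS significantly favoured the customized arm in 53–100%.

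**The case against.** Four points can be made for the plan.

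- **Decay is part of sustainability.** The Objectives section speaks only of sustainability, and change after the end of treatment is a recognised measure of durability. This stands. A reader might infer that the analysis fails to address Objective 2 at all, but the documents do not support that. What the analysis does not test is the fuller hypothesis in the Discussion, which compares retained improvement between sites.
- **Objective 1 would expose an arm that never improved, and the recovery curve shows levels.** This is partly right: the information is in the data, and a careful reader could notice a conflict. However, Objective 1 stops at PA, and two separately reported contrasts do not give the estimate or standard error of their combination. The named between-arm comparison is still the slope.
- **The time model is not stated to be linear.** This is correct. The section refers to a recovery curve and to change up to each follow-up, which is compatible with visit-wise changes. A reader might infer a single straight line dominated by the 6-month visit, but the article does not say so, and the point does not depend on it. Both readings start at PA.
- **This is an unpowered pilot.** The sample size section says so, and the Limitations section calls the efficacy data preliminary. This lowers the severity. It does not remove the mismatch, because the data are meant to inform larger studies.

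**Conclusion.** The point holds. As specified, Objective 2 measures loss of effect after PA and does not test whether improvement is retained to 6 months and is larger at the customized site. That the contrast ignores the level at PA is exact and rests on no assumed figures. That it can favour the arm that is worse at every follow-up is shown by example: +0.26 against 0 points per month, with the customized arm 3 to 5 points better throughout.

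The likelihood of a reversal is unknown. A reader might infer that the trial will report the wrong arm as superior. The documents give no WHODAS means, SDs or decay pattern to support that, and under the assumptions used the chance of a significant reversal runs from about 7% to 86% depending on the scenario. The matter should be fixed, but it is not critical: it concerns the second objective of a pilot that is stated not to be powered.

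**What to change.** Make the main Objective 2 comparison the between-arm difference in WHODAS 2.0 at F1–F4. Fit a mixed model with arm, visit as a category and arm by visit, adjusted for the BL and PS scores. Name one contrast in advance, for example the difference at 6 months or the average over F1–F4; either would serve. Also report each arm's change from the pre-active level at each follow-up. Label this descriptive, because no concurrent sham group exists after PS. Keep the slope or change from PA as a secondary description of durability, read alongside the gain at PA.

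The cost is analysis wording only. Table 2 and the visit description under Data Collection and Measures already schedule WHODAS 2.0 at BL, PS, PA and all four follow-ups. The Results section reports that, as of June 2025, data collection for the randomized phase had not begun. On that status, the contrast could be named before any outcome is seen.

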## Results

As of June 2025, a total of 27 veterans with AUD+mTBI who had been enrolled in the study had completed the neural target identification phase and were awaiting enrollment in the RCT phase. Data collection for the RCT phase will be initiated soon and is expected to be completed by April 2026. We expect the results of this study to be available by May 2026.

## Discussion

### Hypothesized Principal Findings

For objective 1, addressing preliminary rTMS efficacy, we hypothesize that veterans receiving active rTMS at the customized site will have significantly improved functional disability from before to after active rTMS compared to from before to after sham rTMS and compared to the Beam F3 left DLPFC site. This will be indicated by a significantly lower or improved WHODAS 2.0 total complex score from before to after active rTMS compared to from before to after sham rTMS and compared to the Beam F3 left DLPFC site.

For objective 2, addressing rTMS sustainability, we hypothesize that veterans with AUD+mTBI receiving active rTMS applied to the customized site will sustain improvements in functional disability 2 weeks, 1 month, 3 months, and 6 months after active rTMS and that these improvements will be sustained beyond those sustained with rTMS applied to the Beam F3 left DLPFC site.

### Comparison to Prior Work

Research on neuromodulation for a variety of neuropsychiatric conditions is rapidly growing. This study protocol is in line with cutting-edge research that has capitalized on information about functional connectivity and brain state to optimize TMS. Prior work created functional connectivity maps of specific neuropsychiatric symptoms such as PTSD, dysphoria, and anxiety [74,75]. However, to our knowledge, these maps are yet to be tested prospectively as TMS targets in large-scale TMS clinical trials.

Recent research in TMS for SUDs has focused on the salience and ventral attention network, particularly as a potential treatment target [36]. TMS targeting regions that include salience network hubs (eg, the anterior insula and dorsal anterior cingulate cortex) has demonstrated efficacy for smoking cessation [76], leading to the first FDA clearance of TMS for an SUD. There is burgeoning evidence that TMS targeting the salience and ventral attention network could also be promising for AUD [77]. In addition, the frontal pole is another novel potential TMS target for SUDs [78]. As mentioned previously, recent findings indicate that an inhibitory patterned type of rTMS, continuous theta burst stimulation (inhibitory), to the left frontal pole in a single session resulted in reduced alcohol cue–induced brain activation within reward circuitry among people with AUD [79]. Recent results demonstrated improvement for both active and sham TMS groups of frontal pole iTBS groups in reductions in cigarette consumption, cigarette craving, and tobacco withdrawal without between-group effects [80]. Ongoing clinical trials will determine the effects of frontal pole TMS versus left DLPFC TMS for AUD [81]. Thus, this study protocol will contribute to the field and is in line with cutting-edge TMS research.

### Strengths of the Study

To our knowledge, our study is the first to test the efficacy of TMS for individuals with AUD+mTBI, a population with few treatment options. Our study will be of particular significance to the neurorehabilitation field because there is still no consensus regarding the appropriate neural TMS target for SUDs or mTBI individually, let alone AUD+mTBI. Furthermore, although much progress has been made in the TMS neuroimaging field in identifying novel targets and circuits, few studies have directly tested these in comparison to the current clinical standard.

Exploring the preliminary efficacy and sustainability of rTMS effects on functioning, according to a customized AUD+mTBI neural target and the commonly used left DLPFC, is a fundamental first step toward developing and optimizing an rTMS treatment for veterans with AUD+mTBI, for whom there are currently limited treatment options.

We will start the process of developing a customized AUD+mTBI rTMS protocol that is clinically implementable. We will do this comparing the preliminary efficacy and sustainability of the empirically derived rTMS neural target used as a treatment site. Future work will validate the customized AUD+mTBI rTMS site in a larger-scale study examining optimal stimulation parameters and dosing. This line of scientific work will lead to more treatment options for attenuating functional disability among veterans with AUD+mTBI.

### Limitations of the Study

This study may have 3 limitations. First , the single-blind nature of this study could bias results but is also an important step for developing this novel intervention. Future, larger-scale studies should use a parallel-group design and randomly assign participants to sham and active rTMS groups in a double-blinded fashion. Second, the study was powered for the initial TMS target identification phase and not the RCT rTMS treatment phase. In addition, the COVID-19 pandemic significantly affected recruitment. Thus, the RCT rTMS treatment phase could be underpowered. However, the study is intended to provide *preliminary* efficacy data that will serve as foundational work for larger-scale studies. Third, the primary outcome—the WHODAS 2.0—and the secondary outcomes are self-report outcomes that are subjective in nature. However, these measures are standards in the field and encapsulate functional and symptom outcomes that we aim to improve for veterans with AUD+mTBI. Future, larger-scale TMS studies in individuals with AUD+mTBI could add rigor by adding objective measures such as alcohol sensors and clinician-rated functional outcomes that could corroborate patient self-report outcomes.

### Future Work and Dissemination Plan

The next step for AUD+mTBI rTMS treatment development will be to validate whether the customized neural target or site results are generalizable in a larger scale, multisite, randomized, placebo-controlled, double-blind clinical trial. Subsequently, future trials using the validated rTMS site can examine rTMS dosing (eg, 10 vs 20 sessions) or treatment parameters (eg, 10 Hz vs 20 Hz). In parallel, the rich data collected in this study and in future trials can be used to explore which neuroimaging metrics and ARCs are most strongly associated with improvements in functional disability after rTMS treatment. Using big data approaches such as machine learning, the markers of treatment candidacy and the predictors of treatment responsiveness can be evaluated. Once the optimal rTMS neural target, dosing, and parameters are defined and validated, a standardized rTMS protocol can be implemented clinically. This protocol would include the generation of a set of optimal MNI brain coordinates to be used as the rTMS treatment site and a complementary international 10-20 EEG electrode placement site that aligns with the MNI coordinates. If clinical sites are equipped with an rTMS neural navigation system, they can input the MNI coordinates onto the averaged structural T1-weighted MRI scan within the navigation system and then register the patient to this average brain. If clinical sites are not equipped with a navigation system, the EEG placement site can be used instead because using a specific EEG placement method (eg, Beam F3) has demonstrated reasonable approximation to MRI-guided scalp sites for the left DLPFC [82].

We plan to submit the trial results to scientific, peer-reviewed journals; there are no publication restrictions. A CONSORT (Consolidated Standards of Reporting Trials) diagram will be included in the publication. We will follow the International Committee of Medical Journal Editors guidelines for authorship, and there is no intention of using professional writers.

## Appendix

Multimedia Appendix 1

## Abbreviations

ARC: alcohol-related characteristic
AUD: alcohol use disorder
AUD+mTBI: co-occurring alcohol use disorder and mild traumatic brain injury
AUDIT-C: Alcohol Use Disorder Identification Test–Consumption Questions
C-SSRS: Columbia–Suicide Severity Rating Scale
CAPRI: Compensation and Pension Record Interchange
CONSORT: Consolidated Standards of Reporting Trials
DLPFC: dorsolateral prefrontal cortex
*DSM-5*: *Diagnostic and Statistical Manual of Mental Disorders, Fifth Edition*
DTI: diffusion tensor imaging
ED: emergency department
EEG: electroencephalography
EMR: electronic medical record
FDA: Food and Drug Administration
IRB: institutional review board
iTBS: intermittent theta burst stimulation
MNI: Montreal Neurological Institute
MT: motor threshold
mTBI: mild traumatic brain injury
PI: principal investigator
PTSD: posttraumatic stress disorder
RCT: randomized controlled trial
RRT: rapid response team
rs-fMRI: resting state functional magnetic resonance imaging
rTMS: repetitive transcranial magnetic stimulation
SPIRIT: Standard Protocol Items: Recommendations for Interventional Trials
SUD: substance use disorder
VA: Department of Veterans Affairs
VistA: Veterans Health Information Systems and Technology Architecture
WHODAS 2.0: WHO Disability Assessment Schedule
